## 3. MAIN STUDY PREDICTORS (EXPOSURES)

### 3.1 Assessments

We will assess every patient enrolled upon the following predictors.

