Appendix II includes the study clinical outcome definitions.

### **4.3 Feasibility and acceptability outcomes**

The feasibility of frailty assessment will be defined based on the average time and rate of completion of the FP and CFS (and sub-items of the FP). Acceptance of frailty assessment according to physicians will be defined based on ease of use and clinical relevance, according to relevant items of the OADRI. Patient's acceptability of frailty assessments will be measured administering a brief exit questionnaire. Appendix III includes details on how acceptability of frailty instruments from physicians' and patients' perspective will be measured in the study.

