## **5. FOLLOW UP**

### **5.1 Overall study**

Figure 2 shows the study participant timeline.

At baseline (i.e. before surgery, or before NACT for some cases), trained research personnel will collect relevant data about participant demographics, clinical and social history; will administer the WHODAS 2.0 questionnaire and the MoCA; and will assess for frailty. A trained clinical research assistant will measure frailty, first based on the CFS, and then administering the FP tests/questions. In patients undergoing NACT, the study personnel will repeat the frailty, WHODAS 2.0, and MoCA assessments before surgery, after the NACT is deemed to be terminated.

Study personnel will follow patients throughout their time in hospital for surgery, reviewing their medical records and recording any clinical outcome. In hospital, all patients will have troponin measured postoperatively, and then on the 1st, 2nd, and 3rd day after surgery or until discharge, whichever comes first. Data on ischemic symptoms/signs will be collected, and an ECG will be

performed if an elevated troponin measurement is detected. Data on any other troponin measurement that will be undertaken in any study participant within 28 days from surgery will be also collected and will be assessed upon the study definition for MINS. In hospital, study personnel will administer the 3D-CAM twice a day, during the first 3 days after surgery or until discharge, whatever comes first. We will use the CAM-ICU while the patients are in the Post-Anesthesia Care Unit (PACU) or if sent to ICU.

A follow-up study visit will be done at 28 days, 6 months, and 12 months after surgery. Efforts will be made to perform such study visits in concomitance with clinical follow-ups. Frailty assessments will be repeated at 28 days. WHODAS 2.0 will be administered at 28 days, 6 months and 12 months, in-person or over the phone, by research personnel blinded from the frailty assessments. MoCA will be administered at 6 and 12 months (in-person or through videoconference). Study personnel will also collect clinical outcome data through the study follow-ups.

We will also assess physicians' and patients' acceptability of frailty assessments (Appendix III).

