## **6.2 Secondary Analyses**

To compare the predictive performance of different frailty assessments, we will use a similar approach as for the primary outcome, i.e., we will compare the c-statistics of logistic regression models, each including one type of frailty assessment.

To examine the added value of a dynamic perioperative frailty assessment on the primary outcome, we will use a logistic regression model including as predictor with preoperative frailty and change in frailty at 28 days after surgery (either as absolute change and as percent change). The association of frailty with trajectories of disability over the 1 year after surgery will be assessed in a repeated measures linear regression analysis (i.e., mixed effects model); participants who are no longer alive at follow-up will be assigned a score of 100.

Logistic regression or time-to-event models will be performed for the association of frailty and perioperative cardiovascular risk assessment with other outcomes, including chemotherapy-related outcomes, as appropriate.

Effects sizes (odds ratios or hazard ratios) will be presented together with 95% confidence intervals. The threshold for statistical significance will be set as  $p < 0.05$ .

The physicians' and patients' acceptability scores will be compared between frailty instruments using Wilcoxon signed rank tests. The mean and standard deviation (in seconds) required to complete each frailty instrument will be compared using Student t tests; the numbers of missing values will be compared using 2x2 tests.

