#### **Physicians' acceptability**

A convenience sample of 10 consenting physicians involved in the perioperative clinical assessment of the study population (e.g., the Gynecologic Oncology group, the Perioperative Medicine Service, etc.), with no experience with frailty tools, will be invited to participate in the administration of each frailty instrument (FP and CFS). They will be then administered the following questionnaire by research personnel. The questionnaire is a modified version of the OADRI where only items deemed relevant are retained:

The tool is easy to use  
The tool is useful in my practice.  
The wording of the tool is clear and unambiguous.  
My colleagues support use of the tool.  
Patients benefit from use of the rule.  
Using the tool results in improved use of resources.  
The evidence supporting the rule is flawed.  
I'm already using another tool or similar strategy.  
The tool does not account for an important clinical cue.  
The environment I work in makes it difficult to use the tool.

Physicians are asked to rate each item, for each tool, along a 7-point Likert scale including the following options: strongly agree, moderately disagree, slightly disagree, no opinion/don't know, slightly agree, moderately agree, strongly agree.

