#### **Patients' acceptability**

Thirty (30) of the main study participants will be selected according to a purposeful sampling to include patients of different age and different levels of frailty according to the study assessments. At the end of each frailty assessment, they will be asked to complete a questionnaire, which includes 3 closed questions accompanied by 2 open questions:

1. On a scale of 0 to 5, with 0 being not easy at all, and 5 being the easiest, how easy was it to complete the Frailty Phenotype assessment, Clinical Frailty Scale, and Cognitive Frailty questionnaires? You may also answer "no opinion or don't know".
  - a. Can you explain why you find it easy to complete the frailty questionnaire or why you did not find it easy to complete the frailty questionnaire?
2. On a scale of 0 to 5, with 0 being not helpful at all, and 5 being the most helpful, how helpful for understanding your health was it to complete the frailty questionnaire? You may also answer "no opinion or don't know".
  - a. Can you explain why you find it helpful to complete the frailty questionnaire or not helpful to complete the frailty questionnaire?
3. Would you complete the frailty questionnaire again?

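### Completion time and missingness of FP and CFS are paired within patient, but section 6.2 names no paired test for them, and the patient acceptability form does not clearly give a score per instrument

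*Protocol*

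**What the plan says.** Protocol section 3.1 applies the predictors to everyone: "We will assess every patient enrolled upon the following predictors". Section 5.1 puts both frailty tools in one assessment of the same patient: "A trained clinical research assistant will measure frailty, first based on the CFS, and then administering the FP tests/questions". Under section 4.3, feasibility "will be defined based on the average time and rate of completion of the FP and CFS", and of the FP's components.

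Section 6.2 gives the tests. For physicians and patients, "acceptability scores will be compared between frailty instruments using Wilcoxon signed rank tests". For feasibility, the mean time "required to complete each frailty instrument will be compared using Student t tests; the numbers of missing values will be compared using 2x2 tests". The significance level is p < 0.05, with sidedness not stated for these tests.

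Appendix III describes two questionnaires. Ten physicians administer both instruments and rate every item separately for each of them. Thirty patients get three closed questions. The first asks, on a 0 to 5 scale, "how easy was it to complete the Frailty Phenotype assessment, Clinical Frailty Scale, and Cognitive Frailty questionnaires". The second (helpfulness) and the third (willingness to repeat) refer to one frailty questionnaire without saying which. The form is given when each frailty assessment ends. The printed physician scale begins "strongly agree, moderately disagree, slightly disagree" and ends on the same anchor with which it begins.

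**The concern.** Two times and two missing flags from one patient are not independent. A slow or unwell patient is likely to be slow, or incomplete, on both tools. An unpaired t test or an ordinary chi-square test on a 2x2 table ignores this and uses the wrong standard error for the difference between instruments. Because one sentence of section 6.2 names a paired test and the next does not, two analysts could follow the text and report different p-values.

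The acceptability plan has a different problem. A signed-rank comparison of FP and CFS needs two scores from each respondent. If the patient form gives one score for all tools together, there is nothing to pair, and no later choice of analysis can restore what was not asked. Secondary objective 2, the comparison of frailty assessments on feasibility and acceptance, depends on both parts.

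**Working it through.** The protocol states no SD, correlation, missing rate or power for this comparison, so it has no figure to reproduce. The sample size in Appendix I concerns the AUC comparison and does not bear on it. Everything below except n = 280 and the 0.05 level is an assumption, shown as a range. Tests are taken as two-sided.

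**Completion time.** Let the SDs be 1 and k, and the within-patient correlation ρ. For the mean difference, up to the factor 1/n:

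- unpaired variance = 1 + k²
- paired variance = 1 + k² − 2ρk
- SE ratio f = √[(1 + k²) / (1 + k² − 2ρk)]

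For k = 1, f = 1/√(1 − ρ). For k = 4, f = √[17 / (17 − 8ρ)].

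In the normal approximation the true level of the unpaired test is 2[1 − Φ(1.96 f)]. Where a paired test would have 80% power, the unpaired test has power 1 − Φ(1.96 f − 2.80), since 1.96 + 0.84 = 2.80.

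| ρ | f (k = 1) | level | power | f (k = 4) | level | power |
|---|---|---|---|---|---|---|
| 0 | 1.00 | 0.050 | 80% | 1.00 | 0.050 | 80% |
| 0.3 | 1.20 | 0.019 | 68% | 1.08 | 0.034 | 75% |
| 0.5 | 1.41 | 0.006 | 51% | 1.14 | 0.025 | 71% |
| 0.7 | 1.83 | 0.0003 | 22% | 1.22 | 0.017 | 66% |

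Example for ρ = 0.5, k = 1: f = 1/√0.5 = 1.414 and 1.96 × 1.414 = 2.77. The level is 2[1 − Φ(2.77)] = 0.006, and the power is 1 − Φ(2.77 − 2.80) = 51%.

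**Missing values.** This part is a simulation with 280 patients and 20,000 runs. It compares the pooled two-proportion test (chi-square on the unpaired 2x2 table) with McNemar's test, where φ is the correlation between the two missing flags.

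| Missing rates | φ | unpaired rejects | McNemar rejects |
|---|---|---|---|
| 10% and 10% | 0 | 5.0% | 5.0% |
| 10% and 10% | 0.3 | 1.9% | 4.9% |
| 10% and 10% | 0.5 | 0.7% | 5.6% |
| 10% and 5% | 0 | 62% | 62% |
| 10% and 5% | 0.3 | 65% | 78% |
| 10% and 5% | 0.5 | 67% | 91% |

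Both parts agree. Positive correlation makes the unpaired test conservative and less powerful, and zero correlation removes the loss.

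**Acceptability forms against the planned test.**

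- Physicians: each item is rated for each tool, so every physician supplies an FP score and a CFS score. With 10 physicians the smallest two-sided exact signed-rank p-value is 2/2¹⁰ = 0.002, so the test can be computed and can reach 0.05.
- Patients: item 1 puts three named tools under one 0 to 5 rating, and items 2 and 3 name no tool. One completed form therefore holds one ease score and one helpfulness score, not a pair.

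**The case against.** Section 6.2 never says unpaired. A Student t test can be paired, McNemar's test is also a test on a 2x2 table, and the signed-rank sentence may show that the authors know the data are paired. The exact form of a t test is also often left to a statistical analysis plan. This stands in part: what can be shown is an unspecified test whose likeliest reading is unpaired, not a stated error. A reader might infer that the protocol prescribes unpaired tests, but the text does not go that far.

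A reader might also infer that the planned p-values would produce false findings. They would not, because under positive correlation the error runs the other way. Feasibility itself is defined by average time and completion rate, which no choice of test alters, and section 6.2 promises confidence intervals only for odds ratios and hazard ratios.

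The larger SE ratios need equal SDs. That is doubtful here, since the CFS is a single global judgment while the FP includes a grip test, a timed walk and several questions. This objection stands, and it is why the SD ratio of 4 is shown beside the equal-SD case.

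For the patient form, its timing at the end of each assessment could mean that it is repeated after each instrument, which would give pairs. The wording allows this, but item 1 names all the tools together, and section 4.3 calls the form an exit questionnaire. Both count against it. So the form is unclear as worded, not proven unusable.

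Finally, a reader might extend the complaint to the physician form. That is not supported, since its ratings are collected per tool. The repeated anchor is an evident misprint in an ordered seven-point scale.

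**Conclusion.** The point holds in a limited form. That the FP and CFS feasibility data are paired follows from sections 3.1 and 5.1. That section 6.2 fails to name paired tests for them is plain from its text. That the tests would be run unpaired is an inference.

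If they are, the cost is lost power, anywhere from none to large depending on a correlation and an SD ratio that the protocol does not give. At a correlation of 0.5, power where a paired test has 80% would be 51% with equal SDs and 71% with an SD ratio of 4.

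The patient form is the firmer part. As worded it does not clearly yield the FP and CFS scores that the planned signed-rank test compares, and with 30 patients the gap cannot be filled after collection. The primary analysis, its sample size and the other objectives are untouched.

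**What to change.** 1. In section 6.2, state that completion times are compared with a paired t test (or the Wilcoxon signed-rank test) and missing values with McNemar's test. This is a wording change and costs nothing.
2. In Appendix III, ask patient items 1 to 3 separately for each instrument, naming it each time. This costs a revised one-page form and a few extra questions for 30 patients, and must be done before those patients are interviewed.
3. As a minor correction, change the first anchor of the physician scale to strongly disagree.

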## **7.0 SUB STUDIES**

Sub-studies may be added at a later date based on the recommendation of the Project Office Operations Committee. These sub-studies are not part of the main protocol and the analysis and reporting of these sub-studies will be separate from the main study.

## **8.0 STUDY MANAGEMENT**

### **8.1 Arrangements for the day to day management of the study**

The PHRI Project Office is the coordinating centre for this study and is responsible for the development of the protocol, development of the enrollment programming, study database, data consistency checks, data analyses, coordination of the study centres, and conducting the study. The Co-Principal Investigators (co-PIs), Project Officer, Program Manager, and Research Coordinator are responsible for the activities of the Project Office. No statistician with knowledge of the study's protocol will participate in the management or coordination of the FARGO study. Figure 1 describes the proposed phases and associated timelines of the FARGO study. The study will end when all the recruited patients are actively followed for 1-year.

### **8.2 Steering and Publication Committees**

The Steering Committee (SC) will meet at least once if needed during the planning, recruitment, and close-out phases of the study, and at any other time point as deemed necessary by the Chair or study Co-PIs. The SC will provide oversight of all study-related activities and will provide input into protocol development and any revisions, and review all aspects related to study conduct including recruitment rates, adherence rates, completeness of follow-up, and data quality; and to provide recommendations to address concerns. The SC will appoint members to a Publication Committee. This committee will create guidelines for publications related to FARGO. Publications will be authored by specific individuals on behalf of the FARGO Investigators. Individuals selected to lead the writing of these publications will depend on their role in and contribution to FARGO, scientific interest, and scientific expertise.

### **8.3 Site Principal Investigators (PI)**

All participating centres will have a site PI, and this individual is responsible for ensuring compliance with respect to the intervention, visit schedule, and procedures required by the protocol. The site PI will ensure the provision of all information requested in the data collection forms in an accurate and timely manner according to instructions provided. The site PI will maintain patient confidentiality with respect to all information accumulated during the study, other than that information to be disclosed by law.

## **9. ENSURING DATA QUALITY**

### **9.1 Data Management**

Study personnel will complete data collection forms through a program called TrialMaster. Data will be stored on a secure server located at PHRI. Source documentation supporting the information reported on the data collection forms will be filed at the site and made available for monitoring, Institutional Review Board/Independent Ethics Committee (IRB/IEC) review, and regulatory inspections, when required. The Investigator must retain all study records/files in accordance

with applicable regulatory requirements. The Data Management Plan will outline the procedures to ensure data quality and will include the following:

1. All research personnel will undergo a training session before study commencement to ensure consistency in study procedures including data collection and reporting
2. All centres will have a detailed study Manual of Operations that will outline each step of the protocol
3. The Project Office personnel will review detailed monthly reports on screening, enrollment, patient follow-up, data transmission, thoroughness, and completeness of data collection, and event rates, and they will rapidly address any identified issues
4. The programmer will create internal validity and range checks using Trial Master which will identify any errors or omissions and notify the sender and Project Office of any such issues
5. The Project Office will undertake data validation of the study data collection forms
6. The Project Office will send investigators regular quality control reports
7. The study statistician will undertake statistical monitoring to identify outliers

## **9.2 Confidentiality**

All patient information will be stored on a secure server and kept strictly confidential. Patients will be assigned a unique study identification number to ensure anonymity. These ID numbers will correspond to allocation data in secure electronic files.

Centres will be instructed to store any patient information containing names or other personal identifiers separately and identified by their ID number. Centres will secure all local databases with password-protected access systems. Individual subject medical information obtained as a result of this study is considered confidential and disclosure to third parties is prohibited except for the following reason. Medical information may be given to the subject's personal physician or to other appropriate medical personnel responsible for the subject's welfare.

Data generated as a result of the study are to be available for inspection on request by the participating physicians, IRB/IEC, and regulatory authorities.

## **10.0 ETHICAL CONSIDERATIONS**

This study will be conducted in compliance with the protocol, principles laid down in the Declaration of Helsinki, Good Clinical Practice (GCP), as defined by the International Conference on Harmonisation (ICH), and all applicable laws and regulations. Before study initiation, the site PI must have written and dated approval/favorable opinion from the IRB/IEC for the protocol and consent form. Amendments to the protocol will require IRB/IEC approval.

## **11. IMPORTANCE OF THE STUDY**

Little is known about how to best predict postoperative outcomes, recovery from complications, and chemotherapy tolerance in an increasingly older and medically complex GO population. Measuring frailty may represent a comprehensive tool for risk prediction. Our study will 1) help fill the current knowledge gaps; 2) translate into changes in clinical practice, locally, in Canada and potentially worldwide; and 3) inform future studies on shared decision-making and interventions.

# Figures

**Figure 1: Study Flow Diagram**

[figure not shown]

Figure 2 - Study timeline, measurements and data collection

|                                               | Before surgery                        |                                    |                                   | After surgery          |                           |                            |                           |
|-----------------------------------------------|---------------------------------------|------------------------------------|-----------------------------------|------------------------|---------------------------|----------------------------|---------------------------|
|                                               | Patients Not Receiving Chemotherapy   | Patients Receiving Chemotherapy    |                                   | All Patients           |                           |                            |                           |
|                                               | Pre-operative Assessment  | Before chemotherapy  | After chemotherapy  | Day 0 to +3 (+14 days) | 28-Day Visit  | 6-Month Visit  | 1-Year Visit  |
| Patient Consent                               | X                                     | X                                  |                                   |                        |                           |                            |                           |
| Baseline Sociodemographic and Medical History | X                                     | X                                  |                                   |                        |                           |                            |                           |
| Frailty Phenotype                             | X                                     | X                                  | X                                 |                        | X                         |                            |                           |
| Clinical Frailty Scale                        | X                                     | X                                  | X                                 |                        | X                         |                            |                           |
| Cognitive Assessment (MoCA)                   | X                                     | X                                  | X                                 |                        |                           | X                          | X                         |
| Troponin Measurement                          |                                       |                                    |                                   | X                      |                           |                            |                           |
| Disability Assessment (WHODAS 2.0)            | X                                     | X                                  | X                                 |                        | X                         | X                          | X                         |
| Delirium Assessment (3D-CAM)                  |                                       |                                    |                                   | X          |                           |                            |                           |
| Clinical Outcomes                             |                                       |                                    |                                   | X                      | X                         | X                          | X                         |
| Neoadjuvant Chemotherapy-related outcomes     |                                       |                                    | X                                 |                        |                           | X                          |                           |
| Blood Drawing for Biobanking                  | X                                     | X                                  | X                                 |                        | X                         | X                          | X                         |

 Should be done within 45 days prior to surgery  
 Refers to the round of chemotherapy closest to the surgery date  
 Should be done within 30 days prior to chemotherapy  
 Should be done at least 18 days post-chemotherapy cycle and within 45 days prior to surgery  
 Can be done in-person or by telephone/videoconference  
 Should be done twice a day

